### Assessment, care, and trust—In pregnant and new mothers

This questionnaire includes 40 questions to record sociodemographic data, including current residence, education, number of prior pregnancies, the number of biological children (including miscarriages), the number of individuals residing in their home (adults and children), marital status, whether they are living with a partner, basic information concerning the location after the war outbreak and access to support, changes since the beginning of the war, exposure to armed-conflict or limitations to medical support and social support. This questionnaire was created for this study.

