#### Psychometric properties

To examine the psychometric properties of the questionnaires in the Ukrainian language, several analyses will be reported. Exploratory Factor Analyses (EFA) will be conducted using Statistical Package for the Social Sciences (SPSS), Version 26 software. Analysis of the factor dimensional constraints will determine each model’s underlying individual item loadings. Based on the results of the EFA, Confirmatory Factor Analysis (CFA) will then be analyzed. ECA will be used to analyze how to fit the models using several indexes such as Satorra-Bentler χ^2^, CFI, RMSEA and the confidence interval of RMSEA statistics will be calculated. Lagrange multipliers and Wald test will be sequentially performed to improve the models’ fitness, following the study’s hypotheses. Standardized coefficients and measurement equations with scores in R2 will be reported. These analyses will be conducted using the AMOS program.

Prediction models. To examine the risk and protective factors associated with perinatal mental health outcomes, a random sample of 70% of participants will be used to derive the machine learning algorithms, including regularized logistic regression, random forest, decision tree, and gradient boosting to predict the risk of perinatal mental health outcomes, and their performance, and the remaining 30% for validation. First, in the derivation sample, all predictors described above will be included in the models to estimate the probability of depression, anxiety, or PTSD. Beginning with a model containing all potential covariates, the variable with the least significant *p* value will be removed and tested using the likelihood-ratio test until all variables left in the model significantly (at alpha = 0.05) contributed to the model.

In regularized logistic regression models, results will be presented as Odds Ratio (OR) with 95% confidence intervals (CIs).

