Logistic regression analyses will be conducted using the steps forward procedure to examine which variables will predict the study’s dependent variables. This regression analysis makes it possible to predict a dichotomous dependent variable based on predictor, categorical or quantitative variables the R^2^ will be used to calculate the proportion of the explained variance of clinical outcomes by the selected predictors. The different aspects of model performance will be studied. The receiver operating characteristics (ROC) curves (and the corresponding area under the ROC curve—AUC) will also be calculated to test for discrimination characteristics.

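### The AUC and R² of the forward-selected logistic model are not tied to the 30% validation sample; computed in the women used for selection, both are biased upward

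*Protocol article*

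**What the plan says.** The relevant text is the run-in paragraph on prediction models, printed within the Psychometric properties subsection of Data analysis, and the paragraph that follows it.

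- The split is introduced for one family of methods: "a random sample of 70% of participants will be used to derive the machine learning algorithms", "and the remaining 30% for validation". The methods listed are penalised logistic regression, tree-based methods and boosting. The variable removal described there runs backward from a full model, at alpha 0.05, in the derivation sample.
- The next paragraph brings in another model: "Logistic regression analyses will be conducted using the steps forward procedure to examine which variables will predict" the outcomes. This model is not on the earlier list and its selection runs in the opposite direction. No entry level is given.
- Its R² "will be used to calculate the proportion of the explained variance of clinical outcomes by the selected predictors".
- A general sentence follows: "The different aspects of model performance will be studied". The ROC curve and AUC then "will also be calculated to test for discrimination characteristics".

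The second paragraph does not say whether the forward model, its R² or its AUC uses the 70%, the 30% or everyone. It mentions no bootstrap, cross-validation or optimism correction. It also gives no null value, test statistic or confidence interval for the AUC.

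The number of candidate predictors is not fixed. Table 1 lists seven distinct domains from the study questionnaire (pregnancy outcome appears twice). The five personality traits would make twelve. The questionnaire itself is longer: "This questionnaire includes 40 questions to record sociodemographic data".

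**The concern.** Forward selection searches the candidates for those that fit the outcome best in the women at hand, then estimates their weights in the same women. An AUC or R² computed in those women also measures the success of the search. The usual standard error of an AUC assumes a score fixed beforehand, so it makes no allowance for the search.

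The second main goal of the study is to find which risk and protective factors bear on perinatal mental health, and the results are meant to inform policymakers. AUC and R² are the measures that would show how well the selected factors predict depression, anxiety or PTSD. If they come from the selection data, they look favourable to some degree even when no factor predicts anything.

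**Working it through.** **The plan's own figure.** The article states no expected AUC, R² or error rate. Its only related number is the minimum sample size of 300 (Sample size section). With n = 1.96² × 0.5 × 0.5 / e², a margin e of 5% gives 385 and 5.66% gives 300. No margin is stated, so 300 can be neither confirmed nor refuted. It is used here only as an input.

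**Inputs**

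- n = 300, split 210 / 90 (70% / 30%).
- Candidates k: 7 (Table 1 domains), 12 (with the five personality traits), 20 (intermediate), 40 (one per questionnaire item).
- Entry level 0.05. This is an assumption: the article gives 0.05 only for the backward step.
- Outcome prevalence 28%, also an assumption, taken from the 28.2% cited in the Introduction. Values of 14%, 31% and 50% were also run.
- Every candidate is unrelated to the outcome, so the true AUC is 0.50 and the true R² is 0.

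**Step 1: how often noise enters the model.** For k independent candidates, P(at least one enters) = 1 − 0.95^k. This gives 0.302, 0.460, 0.642 and 0.871 for k = 7, 12, 20 and 40. Simulation gave 0.309, 0.443, 0.633 and 0.862.

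**Step 2: same-data evaluation.** Each setting had 1,500 simulated studies with forward score-test entry. The AUC was compared with 0.5 by z = (AUC − 0.5)/SE > 1.96, using the DeLong SE. An empty model counted as AUC 0.5 and no rejection. R² is Nagelkerke's.

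| k | Mean apparent AUC | Mean R² | AUC declared above 0.5 |
|---|---|---|---|
| 7 | 0.53 | 0.010 | 26% |
| 12 | 0.54 | 0.016 | 39% |
| 20 | 0.57 | 0.027 | 57% |
| 40 | 0.61 | 0.055 | 82% |

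The last column can be checked by hand. Once any variable has entered, the comparison with 0.5 (Mann–Whitney null SE) rejects in 83%, 88%, 89% and 95% of studies. Multiplying by Step 1: 0.302 × 0.832 = 25%, 0.460 × 0.878 = 40%, 0.642 × 0.888 = 57%, 0.871 × 0.947 = 82%.

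A second simulation at 25% prevalence gave 27%, 36%, 59% and 86%, with mean AUC from 0.53 to 0.62. The nominal rate in this direction is 2.5%.

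**Step 3: sensitivity**

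- Prevalence matters little: at k = 20 the rate is 57% at prevalence 14% and 59% at 50%.
- Correlation of 0.3 between candidates lowers the k = 20 rate to 50%.
- With half the candidates binary and correlation 0.3, the k = 40 rate is 70% to 76%, depending on the SE.
- Selecting and evaluating both within the 70% does not help: 26% at k = 7 and 83% at k = 40.

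**Step 4: evaluation outside the selection data.** With selection in 210 women and AUC in the other 90, mean AUC was 0.50 in every setting. It was declared above 0.5 in 0.9%, 1.4%, 1.8% and 2.7% of studies for k = 7, 12, 20 and 40. Resampling also works. In 80 datasets at k = 40 and 25% prevalence, the mean apparent AUC of 0.60 fell to 0.48 (bootstrap correction) and 0.50 (five-fold cross-validation), with selection repeated each time.

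**The case against.** The strongest reply is that held-out data exist in the same block of text. The two paragraphs have no heading between them, the list of algorithms is introduced as non-exhaustive, and the performance sentence is general. The ROC/AUC sentence is also the only discrimination measure in the plan; if it served the forward model alone, the validated algorithms would have none. On this reading the error is controlled, as Step 4 shows. This stands as a possible reading, and it is why the rates above are conditional. It does not settle the matter. Nothing confines the forward selection to the 70%, and if selection used all women, the 30% would no longer be untouched. The R² sentence comes before the general one and reads as a fit statistic.

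A reader might also infer that the plan specifies a significance test of AUC = 0.5 that usually succeeds on noise. The document does not support this. It names no such test, and its wording may only mean assessing discrimination. A rate above one half needs roughly 15 to 20 or more candidates: it was 48% at 15 and 57% at 20. With the seven Table 1 domains it is 26%, and with twelve candidates 36–39%.

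The bias is also modest in absolute terms. A mean AUC of 0.53 to 0.62 with R² of 1% to 6% would be read as weak discrimination. That is correct, but it is still discrimination where none exists.

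Finally, an article may leave resampling details to a fuller document. Here, however, it does fix the selection method, the measures and which models the split serves, and the forward model falls outside that assignment.

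**Conclusion.** The point holds as an unspecified evaluation sample with a foreseeable consequence, and is worth correcting. The plan does not state that performance will be judged in the selection data; it leaves that open for the one model outside the list of validated algorithms. If same-data evaluation is used, AUC and R² are biased upward, and a comparison of the AUC with 0.5, if made, would falsely show discrimination in about 26% (7 candidates), 36–39% (12), 57–59% (20) or 82–86% (40) of studies with no true predictor.

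These figures assume n = 300, entry at 0.05, one degree of freedom per candidate and mostly independent candidates. Multi-category items would raise the rates and correlation lowers them. Simulation error is about ±2.5 percentage points.

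**What to change.** In the paragraph on forward logistic regression, state one of the following:

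- the forward selection is run only in the 70% derivation sample, and AUC (with confidence interval) and R² are reported in the untouched 30%; or
- AUC and R² are optimism-corrected by bootstrap or cross-validation, with the entire forward selection repeated in each resample or fold.

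Any claim of discrimination should rest on those values, with apparent values shown only alongside. Listing the candidate predictors and the entry level would also settle how large the search is.

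The cost is one sentence and, for the second option, a short script; no extra participants are needed. Reported AUC and R² will be less favourable. The first option also loses precision. At 28% prevalence, 90 women give about 25 cases and 65 non-cases, so the null SE is √(91/(12 × 25 × 65)) = 0.068, or ±0.13 at 95%. With all 300 (84 and 216) it is √(301/(12 × 84 × 216)) = 0.037, or ±0.07. Resampling uses all the women and avoids evaluating in only 90.

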### Dissemination and data sharing plan

Data and resources obtained and utilized for the study will be made available to other qualified researchers in accordance with academic standards. Those who wish to gain access to the datasets and analyses can do so upon making a legitimate request. The results of the study will be published in peer-reviewed publications and presented at scholarly conferences both domestically and abroad.

## Discussion

The current war in Ukraine affects every other European country in some ways. Since the war outbreak, the neighboring countries have absorbed and registered a high number of refugees on a daily basis (Chrzan-Dętkoś et al., 2022; Kumar et al., 2022; Lloyd and Sirkeci, 2022). Although the number of war refugees varies in European countries, every country faces similar challenges in providing adequate support and possible medical and psychological interventions for women during this vulnerable period; these challenges include language barriers, provision of culturally sensitive services and trauma-informed care, and equitable access to health and mental health services in each European country. Our study aims to assess the mental health needs of perinatal Ukrainian women in their home country and abroad to ascertain the risk and protective factors and the provision of services needed during the perinatal period. Systematic reviews (Hajak et al., 2021) show that migrants who have experienced armed conflict are particularly vulnerable to mental health issues and require mental health assistance. Women in the perinatal period are a vulnerable group, and their mental health may be further exacerbated during wartime.

The midwifery and obstetric care systems in European countries may be an important reference in identifying and caring for those affected. Screening for depression and anxiety with the EPDS and GAD-7, for example, may reduce the disparities observed in the cited literature. Knowing the rate and severity of mental health symptoms and the needs of female war refugees is the first step to creating a plan for helping and preparing services to supply this group of women.

Based on the literature, interventions supporting war-affected mothers and mother—babies dyads should be comprehensive, sustainable, and devoid of harm. Support should be multi-level, resilience-oriented, multidisciplinary, and tailored to the needs of the individual mother (Tol et al., 2011). The Inter-Agency Standing Committee (2007) proposed a multilevel intervention pyramid for mental health and psychosocial support in emergencies, which includes four levels of intervention: (1) provision of basic services and security, (2) community and family support, (3) focused non-specialized support, and (4) specialized support. All layers of the pyramid are essential and should be implemented concurrently according to the needs of the individual. However, to implement it, we need to begin to understand the impact of perinatal mental health of Ukranian perinatal women by investigate prevalence and associated risk and protective factors of mental health problems and the special needs of this target group.

Research shows that many of the European countries do not report specific clinical recommendations or specific guidelines for managing peripartum depression even for women living under normal conditions. Additionally, the existing guidelines vary a lot in the number and themes of clinical recommendations (Motrico et al., 2022). Therefore, the results from this study could assist The European Union and other nations’ policymakers to Create a set of rules and strategies to help reduce the occurrence of mental health issues during pregnancy and childbirth in the Ukrainian crisis and other potential armed conflicts and war-forced migration to EU countries. The United Nations High Commissioner for Refugees (2019) report shows that due to persecution, armed conflicts, deficient healthcare and human rights violations, more than 70 million people worldwide were forcibly displaced from their homes by the end of 2018, with approximately one-sixth seeking protection abroad. Women account for nearly 50% of all refugees, internally displaced, and stateless persons (United Nations High Commissioner for Refugees, 2019). In the literature, we can find interesting reflections focusing on the methodology of studies of immigrants’ mental health. For example, Crumlish and O’Rourke (2010) observed that very few scientists from refugee communities lead research in their communities or the refugee mental health field in general. Planning and implementation of research aimed at understanding these survivors are mainly in the hands of “mainstream academia.” In our study, we could reduce this bias while working in the international team and applying the study protocol together with Ukrainian researchers.

## Conclusion

To sum up, this study is an international research project created to evaluate the effect of the Ukrainian War on the mental health of women during pregnancy. It will allow for a thorough overview of how the war has affected mental wellbeing during the perinatal period, which could then be used to support and guide refugees and providers in different situations. Ultimately, this research should provide concrete data for policymakers and healthcare professionals to utilize.

## Ethics statement

The studies involving human participants were reviewed and approved by Comité de Ética de la Investigación, UNED (Madrid), the Research Ethics Committee of the Faculty of Psychology of Taras Shevchenko National University of Kyiv. The patients/participants provided their written informed consent to participate in this study.

